#### Participants and recruitment

A qualitative online survey will be distributed to patients who are over 18 years of age, are patients who attended the practice for consultation within the 3-month intervention period and for whom a ‘Yes Questionnaire’ is completed. The practice will send an advertisement text message containing a link to the questionnaire to all patients registered to receive text messages from the practice.

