**Methods:**

The primary intervention element, prompted choice, requires general practice to ask patients in consultations if they wish to join the NHS ODR. Two additional intervention techniques will be used to support prompted choice: staff training and leaflets and posters. The intervention will run for 3 months (April–July 2018) followed by a period of data collection. The following methods will be used to assess feasibility, acceptability and fidelity: registration data, a training evaluation survey, focus groups with staff and online surveys for staff and patients.

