*Yes – Selected Organs (prompt will be turned off)*
i.
*Yes - Heart*
ii.
*Yes - Liver*
iii.
*Yes - Kidneys*
iv.
*Yes - Corneas*
v.
*Yes - Lungs*
vi.
*Yes - Pancreas*

*Unsure - Patient will think about it (prompt will appear again at next appointment)*

*Do not ask patient again (prompt will be turned off)*

*Patient believes they are already on the register (prompt will be turned off)*
i.
*Would the patient like to re-register?*

*Yes - All organs and Tissues*

*Yes - Selected organs and Tissues*
i.
*Yes - Heart*
ii.
*Yes - Liver*
iii.
*Yes - Kidneys*
iv.
*Yes - Corneas*
v.
*Yes - Lungs*
vi.
*Yes - Pancreas*

*No - Patient would not like to re-register*

f.
*Patient was not asked*
i.
*Not appropriate for consultation*
ii.
*Lack of time*
iii.
*Clinician personal beliefs (only select if personal view of clinician NOT situational factor)*
iv.
*Other reason, please specify*

If staff member presses ‘No’ on the prompt, this indicates they have not or will not ask the patient to join the NHS ODR. They will then be instructed to complete the following questionnaire which records reason why the patient was not asked.g.
*Patient was not asked. Reason why patient was not asked:*
i.
*Not appropriate for consultation*
ii.
*Lack of time*
iii.
*Clinician personal beliefs (only select if personal view of clinician prevents patient being asked)*
iv.
*Other reason, please specify*

It was highlighted that staff may select the ‘Yes’ questionnaire at the beginning of a consultation but be unable to carry out prompted choice as the consultation progresses. To allow staff to record that the patient was not asked under these circumstances question f. was included in both the ‘Yes’ and ‘No’ questionnaire.

To ensure no untrained staff ask patients about organ donation, the prompt will only appear for staff who have received the training and only for patients aged 18 or over. If prompted choice has previously been completed for the patient and the patient responded “Yes”, “Do not ask patient again” or “Patient believes they are already on the register”, the prompt will switch off and the patient will not be asked again at subsequent appointments.

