### Data collection, management and analysis

Data will be collected in four ways: registration data via the practice computer system, a training evaluation survey, focus groups with staff and patients and an online survey with participating staff.

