#### Materials and procedure

The online survey will be hosted on Qualtrics (2018) [38] and consist of nine open questions and three closed questions. Prior to answering these questions, patients will be presented with an information sheet, consent form and demographic questionnaire. Consent will be gained via ticking boxes on Qualtrics (2018) [38], and the survey should take approximately 10 min to be completed, determined through piloting by the research team.

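### The patient survey's eligibility rule and its text-message distribution do not clearly match, and neither isolates patients who were asked about organ donation

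*Protocol article*

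**What the plan says.** All references are to the protocol article.

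- **Patient online survey, Participants and recruitment.** Besides the age limit, those surveyed "are patients who attended the practice for consultation within the 3-month intervention period and for whom a ‘Yes Questionnaire’ is completed". The following sentence gives the distribution: "The practice will send an advertisement text message containing a link to the questionnaire to all patients registered to receive text messages from the practice".
- **Patient online survey, Materials and procedure.** The survey will "consist of nine open questions and three closed questions". On what comes first: "Prior to answering these questions, patients will be presented with an information sheet, consent form and demographic questionnaire". No eligibility check is mentioned.
- **Intervention, Prompted choice.** Staff may press Yes at the start of a consultation and then be unable to ask. To cover this, "question f. was included in both the ‘Yes’ and ‘No’ questionnaire". Item f records that the patient was not asked.
- **Data collection, management and analysis.** The four data sources include "focus groups with staff and patients and an online survey with participating staff". The patient survey is not listed.
- **Abstract, Methods.** The list there is different: "focus groups with staff and online surveys for staff and patients".
- **Table 1 (SPIRIT figure).** The assessment rows are training evaluation, registration data, focus groups and staff online survey. None is for the patient survey.

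**The concern.** The study's objective includes acceptability, and the Rationale says this means acceptability to patients as well as staff. The staff focus groups cover patient experience only through what staff report. The patient focus groups named in the data-collection list are described nowhere else. That leaves the online survey as the only described direct source of patient views.

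Two things weaken it. First, the eligibility sentence and the distribution sentence can be read as defining different groups, and no step is described that would remove ineligible respondents. Second, the eligibility flag is not a marker of having been asked. Only a patient who was asked can report what being asked was like. If answers from other people enter the framework analysis unmarked, the patient themes on prompted choice, the main intervention element, cannot be attributed to those who experienced it. No link from a survey response back to the SystmONE record is described, so the separation may not be possible afterwards.

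**Working it through.** The plan states no figure for this survey, so there is nothing to reproduce. The check compares the sections and then adds an illustration under stated assumptions.

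**Who would be reached**

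1. Literal reading: every text-registered patient receives the link. This includes non-attenders, attenders for whom staff pressed No, and attenders for whom no form was completed.
2. Channel reading: the link goes to those eligible patients who receive practice texts. Non-attenders drop out.
3. Under both readings, patients "for whom a ‘Yes Questionnaire’ is completed" include those whose completed form carries item f. They were not asked.
4. Neither reading is backed by a described screen: only information, consent and demographics precede the questions.

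**Illustration of size**

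Inputs from the article: about 15,000 patients and about 1,000 consultations a week (Study setting); 5 April to 9 July 2018 and about 10,000 anticipated consultations (Participant timeline, sample size and recruitment). The dates span 96 days, or 13.7 weeks, so the weekly rate gives 13.7 × 1,000 ≈ 13,700. The article's 10,000 is stated to depend on staffing, so both values are carried.

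*Non-attenders.* If every consultation were a different patient, the share of the list that did not attend would be at least (15,000 − 10,000)/15,000 = 33%, or (15,000 − 13,714)/15,000 ≈ 9%. Repeat visits raise both.

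*Patients ever asked.* Assumptions not in the article: a fraction p of consultations leads to asking, and visits per patient follow either a Poisson or a negative binomial distribution with k = 0.5. With m = C × p / 15,000 for C consultations:

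- Poisson: 15,000 × (1 − e^(−m))
- Negative binomial: 15,000 × (1 − (1 + m/k)^(−k))

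For C = 13,700 and p = 0.20, m = 0.1827. Poisson gives 15,000 × 0.167 ≈ 2,504; negative binomial gives 15,000 × 0.144 ≈ 2,163.

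| Consultations | p | Asked: neg. binomial to Poisson | Share of 15,000 |
|---|---|---|---|
| 10,000 | 5% | 476 to 492 | about 3% |
| 10,000 | 20% | 1,672 to 1,872 | 11% to 12% |
| 10,000 | 50% | 3,381 to 4,252 | 23% to 28% |
| 13,700 | 5% | 641 to 670 | about 4% |
| 13,700 | 20% | 2,163 to 2,504 | 14% to 17% |
| 13,700 | 50% | 4,156 to 5,499 | 28% to 37% |

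If text registration is unrelated to having been asked, the last column is also the share of a practice-wide text that would reach patients who were asked. It applies to the literal reading only, and to recipients, not respondents. The number affected by item f under the channel reading cannot be derived from the article.

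**The case against.** The strongest reply is that there is no contradiction. The first sentence already says to whom the survey is distributed, and the second only names the channel: all of those patients who receive practice texts. That reading is reasonable, so it cannot be said that the survey will draw on the wrong people. It does not settle the matter, because the sentence does not limit itself to eligible patients and because item f remains a problem on this reading too.

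Further points, and what stands of each:

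- *A reader might infer that no response rate can be calculated.* The article does not support this. The practice sends the texts, so they can be counted under either reading. What is unstated is which count applies. A response rate also matters less here, since the survey is described as qualitative and its open answers go to framework analysis.
- *A reader might take the data-collection list and Table 1 as further evidence that the wrong people are surveyed.* They bear on whether the survey is listed and when it takes place, not on whom it reaches. They are separate consistency slips.
- *Attenders who were not asked are not unexposed.* Correct: leaflets and posters are part of the intervention, and the survey's aim covers the intervention as a whole. Their views are useful if they can be identified.
- *Self-selection by interest in organ donation.* Any voluntary survey has it, and a filtered list would not cure it.
- *The survey items are not reproduced.* One may already ask about having been asked. Item f is also recorded, so it can be filtered. Both are reasons the repair is easy, not reasons to leave the text as it is.

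**Conclusion.** The concern holds as a risk. As written, the plan allows patients who were never asked, and on the literal reading patients who never attended, to answer the survey with no described way to tell them apart. The flaw in the 'Yes Questionnaire' flag holds on either reading of the distribution sentence.

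The size is not fixed by the article. The 20% asking rate, the visit distributions and the independence of text registration are all assumptions. On them, and on the literal reading, 83% to 89% of those texted would not have been asked, across both consultation counts. On the channel reading only the item f cases remain.

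Severity is moderate. This is a qualitative part of a descriptive, single-practice feasibility study, and the registration analysis is untouched. A reader might infer that the patient acceptability findings are invalid; the article does not show that.

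**What to change.** 1. Reword the recruitment paragraph so that the text goes only to text-registered patients aged 18 or over who attended in the period and have a recorded response a to e, that is, any outcome other than item f. Table 2 already holds a field for whether the patient was asked, so the practice can build the list in SystmONE.
2. Add an opening item on whether the patient was asked about organ donation at an appointment, and use it to screen or route respondents.
3. Report the number of texts sent and the number of responses received.
4. As separate consistency corrections, align the data-collection list with the Abstract, the Staff focus groups section and the Patient online survey section; add a patient survey row to Table 1; and align the survey's 'over 18' with the prompted-choice criterion of 18 or over.

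The cost is a little list-filtering work, one survey item, and fewer but eligible responses. Items 1 and 2 need to be in place before any text is sent, because unscreened responses may not be separable later.

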### Intervention

#### Prompted choice

All clinical staff members (general practitioners, nurses, healthcare assistants and other clinical professionals) working in the practice, who have received training, will aim ask patients during their consultation if they wish to join the NHS ODR. Only eligible patients should be asked based on the following criteria:Inclusion criteria:Patient must be aged 18 years or overPatient must have the capacity to consent2.Exclusion criteria:(c)Patient is under 18 years of age(d)Patient does not have the capacity to consent

Staff will use their professional discretion to determine the capacity to consent and whether it is appropriate to ask the patient the question. They will be trained to limit potential distress by not asking those patients they believe could become distressed due to the content of their consultation. If staff are in any doubt regarding potential distress, they are advised in training not to ask the patient.

A requirement by the NHS REC is that staff must inform the patient that the question is being asked as part of a research study, a scripted question is provided to guide staff. Staff will be prompted to ask the question and to record patient responses using SystmONE, the clinical data system the practice uses. The potential responses for NHS ODR registration are based on the GMS1 form which is completed by new patients to a GP practice. The process of prompting staff and recording patient responses is described below.

Prompt Text.

*“Organ Donation Study.*

*If you will ask the patient to join the NHS ODR please press Yes.*

*If you will not ask the patient to join the NHS ODR please press No.*

*If you would like to ask the patient after the consultation, please press Pause.*

*When you are ready to ask please press ‘Save’ then ‘Resume Protocol’ or ‘Patient -> Resume’.*

*Please do not press the red x.”*

If staff member presses ‘Yes’ on the prompt, this indicates they have or will ask the patient to join the NHS ODR. They will then be instructed to complete the following questionnaire.

*“Eligibility*

*Does the patient have capacity to consent?*

*Yes*

*No (Staff member will be unable to complete the questionnaire if they answer no to this question)*

*Tell the following to the patient:*

*“As part of a research study, I am going to ask you some questions about organ donation.”*
2)
*Patient preferences on joining NHS ODR:*

*Yes – Any of organs and tissues (prompt will be turned off)*

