### Data management

Data will be accessed through SystmONE at the practice by the investigator. Only data relevant to the study (i.e. the data specified in Table 2) will be accessed. Data will be anonymised by the investigator and exported from SystmONE for analysis on an encrypted memory stick. Paper consent forms and training evaluation forms will be stored in a locked filing cabinet at the University of Bedfordshire with access only available to the investigator. These will be stored for 5 years. Online staff survey data will be securely hosted on Qualtrics, who adhere to the data protection act, the general data protection regulation and online data protection procedures. At no point will participants be asked their name, and the only identifiable data collected by Qualtrics will be participants IP address. This will be deleted in all data sets extracted for analysis.

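### The patient survey's text invitation goes to a wider group than its stated eligible population, and no described screen or linkage tells asked from unasked respondents

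*Protocol article*

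**What the plan says.** The Protocol article, Patient online survey, Participants and recruitment, gives two rules in consecutive sentences.

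- **Who the survey is for:** patients over 18 who "attended the practice for consultation within the 3-month intervention period and for whom a ‘Yes Questionnaire’ is completed".
- **Who is invited:** the practice sends a text message "containing a link to the questionnaire to all patients registered to receive text messages from the practice". Nothing narrows this list to the group just defined.

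Under Materials and procedure for the same survey, the steps before the questions are that "patients will be presented with an information sheet, consent form and demographic questionnaire". No eligibility check is mentioned. The survey has nine open and three closed questions, whose content is not given.

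On identifiers, Data management states: "At no point will participants be asked their name, and the only identifiable data collected by Qualtrics will be participants IP address". The IP address is then removed from extracted data. This statement comes directly after one about the staff survey, so its application to patients is an inference. No linkage of patient replies to SystmONE is described anywhere.

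The Prompted choice section adds a complication: "To allow staff to record that the patient was not asked under these circumstances question f. was included in both the ‘Yes’ and ‘No’ questionnaire". A completed 'Yes Questionnaire' can therefore belong to a patient who was never asked.

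**The concern.** The survey's stated purpose is to learn how patients experienced the intervention, and acceptability is one of the study's three objectives. The article lists patients among focus group participants in its data collection overview, but describes a focus group procedure for staff only. The survey is thus the only source of patients' own accounts with a described procedure.

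The framework analysis is to compare themes between patients and staff. If the patient material includes replies from people who never met prompted choice, general opinion about organ donation cannot be told apart from reaction to being asked in a consultation. The findings are meant to inform the later multi-practice feasibility trial. Once anonymous replies are in, the separation cannot be recovered.

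**Working it through.** The plan states no sample size, target number of replies or response rate for this survey, so there is no figure to reproduce. The check compares the two rules and then bounds the mismatch.

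**1. The two rules side by side**

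| Patient group, if registered for texts | Meets the eligibility sentence | Receives the text, read literally |
|---|---|---|
| Adult, attended, 'Yes' form with an answer to the donor question | Yes | Yes |
| Adult, attended, 'Yes' form with option f (not asked) | Yes | Yes |
| Adult, attended, 'No' form or no form | No | Yes |
| Did not attend in the period | No | Yes |

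The third and fourth rows are the contradiction. The second row is a smaller gap: the eligibility rule itself admits some patients who were not asked.

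**2. Lower bound on texts outside the target group**

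Inputs from the article:
- Practice list: about 15,000 (Study setting).
- Consultations: about 10,000 expected over the period (Participant timeline, sample size and recruitment), or about 1,000 a week (Study setting).
- Period: 5 April to 9 July 2018, which is 26 + 31 + 30 + 9 = 96 days, or 96/7 = 13.7 weeks. At 1,000 a week this gives about 13,700 consultations.

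Assumptions: text-registered patients mirror the practice list, and every consultation is a different adult with a 'Yes' form. The second is as favourable to the plan as possible.

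Share outside the target group = 1 − consultations / list size:
- 10,000 consultations: 1 − 10,000/15,000 = 33%.
- 13,700 consultations: 1 − 13,700/15,000 = 8.7%, about 9%.

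Repeat visits, consultations with under-18s or untrained staff, and 'No' forms all raise these figures. If attenders are more likely than others to be registered for texts, the figures fall.

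**3. What can be said about response rates**

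Illustration with assumed inputs: 60% of the list registered for texts, 5% to 40% of those eligible, and 100 replies.
- Texts sent: 0.60 × 15,000 = 9,000. Crude rate: 100/9,000 = 1.1%, which is computable.
- Eligible patients invited: 0.05 × 9,000 = 450, to 0.40 × 9,000 = 3,600. The practice could count the true number in SystmONE.
- Rate among eligible patients: from 0 up to 100/450 = 22% in the first case, and from 0 up to 100/3,600 = 2.8% in the second. The numerator is unknown because eligible respondents are not identified.

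**The case against.** The strongest reply is that the second sentence only names the delivery channel: the survey goes to the eligible group, and those of them registered for texts receive one. The wording permits this but does not say it, and a practice following the sentence as printed would text its whole list.

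A second reply is that a screen may sit in the information sheet, the consent form, the demographic questions or the closed questions, none of which is shown in a condensed article. That stands as a limit: the ability of unasked patients to answer is inferred from the steps described. It does not remove the conflict between two rules that the article does state.

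Third, leaflets and posters are part of the intervention, so attenders who were not asked did meet one component. That is a reason to report their views separately, not to pool them with views on prompted choice.

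Three stronger readings are tempting and are not supported:
- **That no response rate is possible.** Texts can be counted, and so can eligible text-registered patients. No response rate is planned, and the stated aims of the later trial do not call for one.
- **That the great majority of texts go to ineligible people.** This needs a visit frequency and an asking rate that the documents do not give.
- **That the text breaches a protection for vulnerable patients.** Staff are trained to limit distress by "not asking those patients they believe could become distressed due to the content of their consultation". That ties the decision to a particular consultation. Not being asked is not among the responses listed as switching the prompt off, and posters are on open display. An optional survey link is not shown to breach the rule.

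**Conclusion.** The point holds as a contradiction between the stated survey population and the stated invitation list. Followed literally, it invites people who did not experience prompted choice, and nothing described separates their replies. The consequences are possible contamination of the patient acceptability data and an unknown response rate among eligible patients.

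The size cannot be determined from the documents. The 9% and 33% figures are minimum shares of texts outside the target group under the two consultation totals that the plan supports. Both depend on the text list resembling the practice list. They describe invitations, not replies: people who were never asked may be less inclined to respond.

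The conclusion would fall away if the sponsor's full materials show that the text list is filtered, and would be largely met by an exposure screen in the survey. In either case the article's wording should still be clarified.

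**What to change.** Reconcile the two sentences. Have the practice draw the text list from SystmONE, limited to text-registered adults who attended in the period and whose 'Yes Questionnaire' records an answer to the donor question. This excludes forms completed with option f. The search needs only whether an answer was recorded, not which answer.

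Add one opening item asking whether the patient was asked about the register during a consultation. Route out those who say no, or report their replies separately if views on the leaflets and posters are wanted. Record the number of texts sent, so that a response rate among eligible patients can be reported.

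The cost is one practice search and one extra item. Fewer invitations go out, so there may be fewer replies. Separate links by recorded donor decision, or a demographic comparison of respondents with all asked patients, are optional and not needed to cure the defect. Sorting texts by decision would also be a new use of data collected without individual consent, and would need its own justification.
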